#### 40 m Fast-paced Walk test

The purpose of the 40 m fast-paced walk test is to assess short distance walking ability [29]. The test measures the time, in seconds, taken to walk 40 m as quickly but as safely as possible excluding turns. The total time is expressed as m/s by dividing distance (40 m) by time (seconds). Any gait aids required are recorded [48]. The reliability and validity of the 40 m fast-paced walk test has been tested in a group of combined pre-operative THA and TKA patients, where test-retest reliability was found to be excellent, ICC _(2,1)_ = 0.91 (95 % CI = 0.81-0.97) and responsiveness to initial surgery followed by recovery was evident [38] Standard error of measurement (SEM) was calculated as 1.73 (95 % CI = 1.39-2.29) and minimal detectable change at the 90 % confidence level (MDC_90_) was 4.04 sec [38].

#### 30-second chair stand test

The 30-second chair stand test (30s CST) is a test of sit-to-stand ability, lower limb strength and dynamic balance [29]. Starting from a seated position, the patient stands then sits as many times as possible in 30 seconds [49]. The chair is a straight back chair with a 44 cm seat height, preferably without arms. If the patient cannot stand without using their arms, their hands can be placed on their legs and recorded as an adapted test score [29]. An initial practice trial will be performed to reduce any practice effect [50]. In a population with end stage hip or knee OA awaiting joint replacement surgery, intra-tester reliability (ICC _(1,1)=_ 0.97-0.98, 95 % CI = 0.94-0.99) and inter-tester reliability (ICC _(1,1)_ 0.93- 0.98, 95 % CI = 0.87-0.99) were excellent [50]. Convergent validity was evident by a moderate correlation (Spearman’s rho = 0.64 (95 % CI 0.49 to 0.75)) with other measures of physical function. Discriminant validity was evident by low correlation (Spearman’s rho = 0.33 (95 % CI 0.12 to 0.51)) with mental health scores. Known groups validity was demonstrated by significantly higher scores recorded for participants who ambulated without a gait aid compared to participants who did not with a mean difference of 2.8 (95 % CI 1.4 to 4.1) and effect size of 0.64 (95 % CI 0.32 to 0.95). Standardized response mean of 0.84 (95 % CI 0.61 to 1.07) indicates the 30s CST is a responsive measure [51].

#### Step test

The step test is a functional, dynamic test of standing balance [52] which has been commonly used to measure outcome of interventions in patients with OA knee [53–57]. This test is used to assess the ability of the patient to maintain standing balance whilst performing a potentially destabilizing movement [58]. The step test involves stepping one foot on, then off, a block as quickly as possible in 15 seconds without holding a support. The same procedure is then repeated with the opposite leg stepping [52]. It has high test-retest reliability in healthy older subjects (ICC > 0.90), good concurrent validity and is sensitive to changes in performance over time [52].

### Isometric strength quadriceps muscle

Isometric quadriceps strength will be measured against a strap and HHD with the patient sitting and the knee at 90° flexion [59]. Isometric quadriceps strength has been tested at knee flexion angles of 45-90° [60] and is recommended to be tested at 60-90° knee flexion [61]. Isometric quadriceps strength measured with HHD at 90° knee flexion has demonstrated excellent reliability (ICC _(2,1)_ = 0.96) and MDC_95_ of 0.58 N/kg following TKA [59]. If the participant cannot flex their knee to 90°, isometric quadriceps strength will be measured at the maximum range of flexion available and the range will be recorded. The hand-held dynamometer (HHD) will be placed on the anterior aspect of the distal tibia, 5 cm proximal to medial malleolus. Stabilization of the HHD will be achieved by wrapping a seatbelt around the HHD and securing it to a fixed attachment of the plinth. The participants will perform a maximal voluntary isometric contraction (MVC) by extending their lower leg against the dynamometer and seatbelt, held for 5 seconds. The highest of three consecutive measures will be recorded as the MVC.

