### Interventions

#### Usual care

All participants in this trial will participate in the usual care structure of rehabilitation at the treating institution. Under the usual care rehabilitation, inpatients at the hospital with TKA attend either two 45-min sessions of physiotherapy or one 45-min session of physiotherapy and one 45-min session of hydrotherapy every day on five days of the week. All participants also attend one 45-min session of either physiotherapy or hydrotherapy on the other two weekend days. All patients at the rehabilitation hospital receive hydrotherapy unless the surgeon recedes permission, or for health or personal preferences of the patient. The hydrotherapy exercises use water resistance, buoyancy and hydrotherapy equipment to achieve the same goals as the land-based therapy. Patients who do not receive hydrotherapy will attend an additional session of land-based physiotherapy, meaning that all patients receive exercise therapy twice a day. Participants will be given a home exercise program to be completed following discharge from inpatient rehabilitation. The home exercise program will be identical to the exercises performed during inpatient rehabilitation. Exercise dosage will be recorded in an exercise diary.

Participants will return to the rehabilitation hospital to participate in the outpatient rehabilitation program approximately one week following discharge from inpatient rehabilitation. All participants will attend once per week for one 45-min session of physiotherapy and either one 45-min session of hydrotherapy (if indicated) or land-based exercise (if hydrotherapy not indicated). These two 45-min sessions will occur consecutively on the same day of each week. Participants will continue their home exercise program and complete their diaries daily.

The exercises in the usual care rehabilitation program are representative of usual care following TKA, and are described in detail in Table 1 and in the Additional file 1. The goals of the usual care rehabilitation program are to improve quadriceps, hamstring and calf strength, to increase knee range of movement and to improve walking and stair climbing ability. Manual therapy including joint mobilization and massage may also be used in addition to exercises to achieve these goals.

**Table 1 Tab1:** Usual Care Exercises

Goal	Exercise
Improve quadriceps strength	Static quads
	Quads over fulcrum
	Forward step-ups
	Squats
	Leg press
	Forward step-downs

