Primary and secondary outcomes will be measured at admission to inpatient rehabilitation (approximately 7 days post-operatively), 3 weeks, 6 weeks and 6 months after commencing the rehabilitation program. A discrepancy is often reported in the recovery of patient reported outcomes compared to functional performances, with the more rapid improvement noted in patient reported outcome scales while functional performance measures are often significantly reduced in the early post-operative period [30]. Therefore, the two types of outcome measures have been included to ensure an accurate representation of rehabilitation outcomes following TKA.

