A second limitation of the study is a lack of pre-operative testing of hip abductor strength as well as other outcome measures, which would add value to the study. However, the patients that require inpatient rehabilitation in this study are not identified pre-operatively. The need for inpatient rehabilitation is identified post-operatively on an individual basis and outpatient rehabilitation is determined on arrival to the rehabilitation hospital. The lack of pre-operative testing is taken into account by measuring the hip abductor and quadriceps muscle strength at all time points in the study. The recovery of muscle strength in both groups can then be compared and their contribution to functional gains calculated.

The exercise programs described are standardized by guidelines for progression according to the American College of Sports Medicine (ACSM) guidelines [28]. Progression of exercises will also be based on the physiotherapists’ clinical assessment and tailored to the individual participants needs. The usual care exercise program has additional functional exercises to account for the extra time spent on hip strengthening exercises by the hip strengthening group participants. The use of additional manual therapy will also be decided for individual participants according to their clinical need.

There is a need for more knowledge regarding specific hip strengthening compared to usual care following TKA. The findings of this study will guide clinicians regarding the use of hip strengthening exercises in TKA rehabilitation programs.

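### Quadriceps force is tested at the flexion the knee can reach when tested, up to 90°, so for knees below 90° at admission the change over time mixes strength with joint position

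*Protocol article*

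**What the plan says.** All of the following is in the protocol article.

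- **Isometric strength quadriceps muscle:** force is "measured against a strap and HHD with the patient sitting and the knee at 90° flexion". The exception begins "If the participant cannot flex their knee to 90" degrees; in that case "isometric quadriceps strength will be measured at the maximum range of flexion available and the range will be recorded". No lower limit is set, and nothing requires later visits to reuse the participant's first angle. The section also notes that testing has been done at 45° to 90° and "is recommended to be tested at 60-90° knee flexion". The cited ICC of 0.96 and MDC95 of 0.58 N/kg belong to the 90° position: "Isometric quadriceps strength measured with HHD at 90° knee flexion has demonstrated excellent reliability".
- **Outcome measures:** quadriceps strength is a secondary outcome, in Newtons (Table 4). Outcomes are "measured at admission to inpatient rehabilitation (approximately 7 days post-operatively), 3 weeks, 6 weeks and 6 months after commencing the rehabilitation program".
- **Usual care:** the goals for all participants include "to increase knee range of movement and to improve walking and stair climbing ability".
- **Data and statistical analysis:** every outcome goes into a group-by-time repeated measures ANOVA over the four assessments, giving main effects and the interaction. No role is stated for the recorded angle.
- **Discussion:** because there is no pre-operative test, hip abductor and quadriceps strength are measured at every time point. "The recovery of muscle strength in both groups can then be compared and their contribution to functional gains calculated".

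**The concern.** The force a muscle registers in an isometric test can depend on joint angle as well as strength. A test repeated over time therefore measures change in strength only if the angle is held. Here it is held for participants who reach 90° at every visit. For those who do not, the angle is tied to knee range, which the rehabilitation in both arms is meant to increase. Test position then moves systematically with time since surgery.

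Two uses of the measure are exposed even if both arms regain range equally. The first is the main effect of time and any within-arm account of strength recovery. The second is the planned link between strength recovery and functional gains: if the strength change carries recovery of knee range inside it, an association with function could partly reflect range.

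**Working it through.** The plan gives no figure on this point. Its only design calculation, a minimum of 82 participants, does not depend on the test angle. The check is therefore a reading of the rule plus an illustration on assumed inputs.

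**1. Can the angle change within a person?** Yes. The angle is 90° or, failing that, the maximum available when tested. The first test is about 7 days after surgery and increasing range is a treatment goal. A participant below 90° at admission who gains range is tested at a larger angle later. One who is at 90° throughout is unaffected.

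**2. What does that do to one person's change?** Let S1 and S2 be true strength at two visits, expressed as force at 90°. Let r be force at the lower angle divided by force at 90°, with S2 measured at 90°.

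- Under the plan: observed ratio = S2 / (r × S1) = (S2/S1) / r.
- With the baseline angle repeated: observed ratio = (r × S2) / (r × S1) = S2/S1, so the angle cancels. This assumes that r is stable over time.

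With S2 = S1, the plan's rule shows an apparent change of 1/r - 1. For r = 0.8 this is +25.0%; for r = 1.3 it is -23.1%. The range spans both sides of 1 because the documents do not give the direction.

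**3. What does it do to the mean over time?** Let q be the share tested below 90° at baseline, all reaching 90° later. True strength is constant and equal on average in affected and unaffected participants.

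Apparent mean change = 1 / (q × r + 1 - q) - 1

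| q (assumed) | r = 0.8 | r = 1.3 |
|---|---|---|
| 0.1 | 1/0.98 - 1 = +2.0% | 1/1.03 - 1 = -2.9% |
| 0.3 | 1/0.94 - 1 = +6.4% | 1/1.09 - 1 = -8.3% |
| 0.5 | 1/0.90 - 1 = +11.1% | 1/1.15 - 1 = -13.0% |

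**4. What does it do to the arm contrast?** At one visit, mean force in an arm is proportional to 1 - q + q × r. The artefact in the difference between arms is therefore dq × (r - 1), where dq is the difference between arms in the share below 90°.

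- dq = 0: 0 × (r - 1) = 0.
- dq = 0.1: 0.1 × (0.8 - 1) = -2% to 0.1 × (1.3 - 1) = +3%.

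So balanced arms have no systematic artefact, only extra variation between participants in measured change. Bias needs a difference between arms in range recovery.

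**5. Could the analysis repair it?** Only in part. The recorded angle allows adjustment, or an analysis restricted to tests at 90°. But within a person the angle rises with time, so adjustment needs a model for the angle effect, and restriction drops the early visits of the stiffest knees. Neither supplies a same-angle measurement that was not taken.

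**The case against.** **Randomisation and the angle record.** Arms are randomised, both receive the same range exercises, and the angle is recorded. How it is used may be set out in an analysis plan that is not shown, so the article's silence on adjustment is no error. This stands, and it is why the point concerns the measurement rule and mainly the time effect, not the arm contrast.

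**The remedy has a trade-off.** Under the current rule knees tend towards 90°, the only position with cited reliability. Holding stiff knees at their baseline angle moves angle differences from within persons to between persons for the whole trial. That is true of absolute values. It does not undermine change over time: the baseline angle is set at admission, and differences in it between people are balanced in expectation by randomisation. Keeping the 90° test as well preserves the common-angle value.

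**Stronger readings that a reader might infer, and that the documents do not support:**

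- *The arm comparison is biased because the control arm's sit-to-stand and marching work the knee more than the hip exercises do.* The exercise lists differ, but nothing shows that range recovers differently.
- *The test falls outside the recommended range.* The rule would permit angles below 60°, but nothing indicates that participants would be there, and the same sentence reports testing from 45°.
- *The artefact is a large fraction of the MDC95.* That needs a body weight, a force and an angle effect that the documents do not give. The MDC95 is also a threshold for individual change, not for a group difference.
- *The whole strength-recovery comparison rests on this measure.* Hip abductor strength is a primary outcome and is tested in a fixed neutral position.

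**Conclusion.** The point holds in a limited form. The testing rule lets the angle rise across visits for participants below 90° at admission, so their change in quadriceps force is partly a change of position. The time effect and the strength-recovery and strength-function statements are exposed. The arm contrast gains noise, and bias there is possible but not shown.

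The size cannot be fixed from the documents. The illustration (+6.4% to -8.3% at an assumed 30% affected and an assumed force ratio of 0.8 to 1.3) shows only that the artefact need not be trivial and could go either way. If few participants start below 90°, it is small.

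This is one secondary outcome, and neither primary outcome is touched. The change is still worth making, because later analysis cannot fully repair it and the cost is low.

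**What to change.** Add to the quadriceps test procedure:

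- A participant who cannot reach 90° at admission is tested at every later visit at the angle recorded at baseline, set with the goniometer already used for knee range. This same-angle force is the value used for change over time.
- Once 90° is reachable, the participant is also tested there and the value is reported, since the cited ICC and MDC apply only to that position.

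The cost is a sentence or two in the procedure, setting the angle before the test, and a few extra contractions for the affected participants. The downside is that their same-angle values are not directly comparable in absolute terms with values taken at 90°.

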### Passive knee range of movement (PROM)

Passive knee ROM will be measured with a goniometer axis placed at the lateral epicondyle of the femur, the proximal arm parallel to the long axis of the femur & pointing at the greater trochanter, the distal arm parallel to the long axis of the fibula and pointing at the lateral malleolus. Maximum passive flexion and maximum passive extension range of movement will be recorded.

### Lower Extremity Functional Scale (LEFS)

The Lower Extremity Functional Scale (LEFS) is a 20-item self-report measure of lower extremity functional status. Each item is scored on a 5-point scale (0–4) and the total LEFS scores ranges from 0 to 80 with higher scores reflecting greater levels of functional status [62]. Test-retest reliability has been reported as excellent (ICC _(2,1)_ = 0.85), SEM = 3.7 points and MDC_90_ = 9 points in a combined group TKA and THA [43, 63–66]. Internal consistency was reported as 0.93 while cross sectional validity (r = 0.68) and longitudinal validity (r = 0.64) were also good [63].

### SF-12

The SF-12 is a generic measure of a patient’s general physical and mental well-being [67] based on the SF-36 score [68]. Patients’ general and physical wellbeing can influence the outcome of joint-specific scores following TKA [69]. The SF-12 has been used extensively to measure outcomes following TKA [69–75]. Reliability coefficients of 0.84 and 0.80 were observed for the physical component and mental components respectively in a pre-operative TKA population [76]. The level of patient satisfaction with TKA patients’ pain relief and function correlated with the improvement in the physical component of the SF-12 score (r = 0.51, *P <* 0.001 and r = 0.60, *P <* 0.001) respectively. The minimal clinically important difference (MCID) for the physical component of the SF-12 was 4.5 points (95 % CI = 3.9 to 5.2) and 4.8 points (95 % CI = 4.2 to 5.4) for pain relief and function component respectively [77].

### Other measures

#### Compliance

Compliance will be assessed by review of the patient notes recorded by the treating physiotherapist. These notes will be assessed for the type of exercise, dosage of exercises and adverse events for each treatment session. On discharge from inpatient rehabilitation patients will be given an exercise diary, which will record the dosage of each exercise and any adverse events experienced daily.

#### Adverse effects

Any adverse responses will be noted in the patient notes located in the patient’s hospital file. The physiotherapists will be trained to recognize adverse events such as significant increases in knee pain, lateral hip pain in the training session held prior to the commencement of the trial.

#### Type of TKA

Details will be taken from operation report or contact with the surgeon if not recorded on operation report. The surgical approach, presence of patellar resurfacing, type of prosthesis including cruciate retaining, posterior stabilized or other, will be recorded.

#### Data and statistical analysis

An estimate of sample size was made on the ability to detect a medium effect (Cohen’s f = 0.25). The assumption of obtaining a medium effect size was reasonable based on the effect sizes reported for similar measures such as the WOMAC by other studies in the literature (effect size for WOMAC function = 0.3, WOMAC pain = 0.31) [18]. A standard statistical package was used [78]. To obtain a power of 0.8 at a significance level of α = 0.05, a minimum sample of 82 participants would be needed. To allow for loss to follow-up the aim was to recruit a sample of approximately 104 participants.

Participant characteristics and baseline data will be summarized by descriptive statistics. Independent sample t-tests for parametric data (or a chi-squared test for categorical data) will be used to determine the comparability of the two groups at baseline on measures of age, gender and BMI. All data will be analysed using intention to treat principles. Any missing data will be replaced by the last observation carried forward. Repeated measures ANOVA (group by time) calculations will be used to determine the main effects and interactions of group (hip abductor strengthening vs usual care exercises) and time (repeated factor: baseline, 3 weeks, 6 weeks, 6 months) for all outcome measures. Statistical analysis will be completed using SPSS software (version 22) and the significance level set at *P <* 0.05.

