### Randomisation and allocation concealment

Eligible patients will be identified by the treating physiotherapist. The treating physiotherapist will inform the patient of the study, give them the patient information sheet and arrange for a meeting with the primary researcher. The primary researcher will discuss any questions with the patient and gain informed consent of willing participants. Eligible patients will be randomized by a computer-generated list of random numbers to usual care or usual care plus hip strengthening. An independent person, not involved in delivering the intervention or testing, will manage the allocation list and numbered opaque envelopes containing the allocated group of each participant. Only the treating physiotherapist will be informed of the group allocation of the participants. The allocation list will not be available to the researchers and the participants will not be informed which group they are in. The participants will be informed that there are two different rehabilitation programs but will not be told that one program is specifically targeting hip strengthening exercises. This is to prevent potential bias from knowledge of treatment. The rehabilitation will be conducted in a large busy gym where there are many different patients with different diagnoses treated at the same time by their individual physiotherapists with individual exercise programs dependent on each patient’s needs. This will reduce the probability of patients from one intervention seeing the other intervention group’s exercises. A survey on exit from the study will be conducted to determine which group the participants thought they were in during their rehabilitation.

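### The 80% power at N = 82 fits a group main effect that counts baseline as a treated visit; for a medium effect arising after baseline, that planned test has about 44–68% power at N = 82

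*Protocol article*

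**What the plan says.** All of this is in the protocol article under Data and statistical analysis, unless noted.

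- Effect size: "An estimate of sample size was made on the ability to detect a medium effect (Cohen’s f = 0.25".
- Sample size: "To obtain a power of 0.8 at a significance level of α = 0.05, a minimum sample of 82 participants would be needed".
- Software: "A standard statistical package was used [78". No test, number of measures or correlation is given with it.
- Recruitment: "To allow for loss to follow-up the aim was to recruit a sample of approximately 104 participants". The implied loss is 1 − 82/104 = 21%.
- Analysis: "Repeated measures ANOVA (group by time) calculations will be used to determine the main effects and interactions of group", with "time (repeated factor: baseline, 3 weeks, 6 weeks, 6 months) for all outcome measures". Baseline is thus one of the four levels of the time factor.
- Missing data: "Any missing data will be replaced by the last observation carried forward".
- Allocation (Randomisation and allocation concealment): "Eligible patients will be randomized by a computer-generated list of random numbers to usual care or usual care plus hip strengthening".

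Trial design and Outcome measures place the baseline assessment at admission to inpatient rehabilitation, before the programme can act.

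**The concern.** A group main effect in a repeated-measures ANOVA compares the two groups on the average of all visits in the time factor. If 82 was obtained for that test, the calculation assumed the full medium difference at each of four visits. At one of them, baseline, randomisation makes the expected difference zero. A treatment effect that starts after baseline is therefore diluted in the average that the ANOVA tests.

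What is at stake is how a null result would be read. The trial is meant to tell clinicians whether to add hip strengthening. If the power for a medium treatment effect is well below 80%, a non-significant group effect is weaker evidence of no benefit than the protocol implies.

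**Working it through.** **Inputs.** From the protocol: f = 0.25, α = 0.05, power 0.8, N = 82 (104 recruited), two groups, four visits. Assumed, because not stated: 1:1 allocation, equal variances, and one common correlation ρ between visits (compound symmetry), varied from 0.3 to 0.8. With two equal groups, d = 2f = 0.5. Power is from the noncentral F distribution.

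**Step 1: reproduce 82.** For the group main effect over m visits, λ = f²·N·m / (1 + (m − 1)ρ), with 1 and N − 2 df. With m = 4 and ρ = 0.5:

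- N = 82: λ = 0.0625 × 82 × 4 / 2.5 = 8.2, power 80.8%.
- N = 80: λ = 8.0, power 79.8%.

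So 82 is the smallest N in equal groups. With the same inputs, the group-by-time interaction needs 24 and a single-visit comparison needs 128.

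**Step 2: put the effect after baseline.** Let the true differences be (0, 0.5, 0.5, 0.5) SD. Their average is 0.75 × 0.5 = 0.375 SD. The variance of a participant's four-visit mean is (1 + 3ρ)/4.

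- Main effect: λ = (N/4) × 0.375² / [(1 + 3ρ)/4]. At N = 82 and ρ = 0.5, λ = 20.5 × 0.1406 / 0.625 = 4.61 on 1 and 80 df, power 56.4%.
- Interaction: the squared deviations of the four differences from 0.375 sum to 0.1406 + 3 × 0.0156 = 0.1875. λ = (N/4) × 0.1875 / (1 − ρ). At N = 82 and ρ = 0.5, λ = 20.5 × 0.1875 / 0.5 = 7.69 on 3 and 240 df, power 62.7%.

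A simulation of 20,000 trials gave 56.6% and 63.4%.

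**Step 3: vary the correlation.**

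| ρ | Main effect, N = 82 | Main effect, N = 104 | Interaction, N = 82 | Interaction, N = 104 |
|---|---|---|---|---|
| 0.3 | 68% | 78% | 47% | 58% |
| 0.4 | 62% | 72% | 54% | 66% |
| 0.5 | 56% | 67% | 63% | 74% |
| 0.6 | 52% | 62% | 73% | 84% |
| 0.7 | 48% | 58% | 86% | 93% |
| 0.8 | 44% | 54% | 97% | 99% |

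The main effect is below 80% in every row. The interaction reaches 80% at ρ of about 0.65 for N = 82 (79.6% there), and just under 0.6 for N = 104. The N = 104 columns assume that everyone is analysed with the full effect. Carried-forward early values would dilute it.

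**Step 4: what would make 80% true.** For the four-visit average to be 0.5 SD with zero at baseline, each follow-up difference must be 0.5 × 4/3 = 0.67 SD. Main-effect power at N = 82 and ρ = 0.5 is then again 80.8%, and interaction power is 88%.

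**Step 5: a slower effect.** If the difference grows in equal steps to 0.5 SD at 6 months (0, 0.17, 0.33, 0.5), power at N = 82 and ρ = 0.5 is 29% (main effect) and 49% (interaction).

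**Step 6: baseline as covariate.** λ = (N/4) × 0.25 / residual variance, with 1 and N − 3 df. At ρ = 0.5:

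- Mean of three follow-ups: residual variance (1 + 2ρ)/3 − ρ² = 0.667 − 0.25 = 0.417. At N = 82, λ = 12.3, power 93%.
- 6 months alone: residual variance 1 − ρ² = 0.75. At N = 82, λ = 6.83, power 73%. At N = 104, λ = 8.67, power 83%.

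Over ρ from 0.3 to 0.8, power for the follow-up mean is at least 92% at N = 82. For 6 months alone it runs from 65% to 96% at N = 82 and from 75% to 99% at N = 104.

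**The case against.** The strongest reply is that 82 is not an arithmetic error. It reproduces, and for the literal input, f = 0.25 as the four-visit average, it delivers 80.8%. That stands. The shortfall comes from reading the medium effect as the difference after treatment begins. That is the natural reading of a treatment effect, but the protocol does not define f this way. Nor does it argue for the 0.67 SD that the other reading requires.

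A reader might go further and infer three things that the document does not support.

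- *That 82 can only come from this calculation.* The test family is not stated, and other routes also give 82: a main effect over three measures at ρ = 0.45, a three-measure interaction with f taken from partial eta-squared, or a single-visit ANCOVA with correlation 0.6. None of these is the planned four-visit ANOVA. If one was used, the planned main effect would still contain baseline. That the article does not name the test or correlation is not a fault in itself, since such detail may stand in a fuller document.
- *That the trial simply has 56% or 63% power.* Those figures hold at N = 82 and an assumed ρ of 0.5. With all 104 analysed they are 67% and 74%. The plan keeps dropouts in by carrying values forward, so 104 is relevant, though as an upper bound.
- *That both planned tests fall short.* The interaction, which tests whether the groups change differently over time, reaches 80% or more at higher correlations. Its shortfall is not established.

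**Conclusion.** The point holds in a conditional form. If f = 0.25 describes a 0.5 SD difference present from the first follow-up onwards, the planned group main effect does not have the stated 80% power at any correlation from 0.3 to 0.8. The chance of missing such an effect with that test is 32–56% at N = 82 and 22–46% at best with 104, against the 20% implied. The direction does not depend on the unknown correlation within this range, because the cause is structural: an untreated visit is averaged in. The interaction may or may not fall short, depending on the correlation.

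The conclusion rests on 1:1 allocation, compound symmetry and a constant effect after baseline. An effect that builds up gradually makes the main-effect power lower still.

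**What to change.** State which contrast f = 0.25 refers to, and restate the power for that contrast. Give the number of visits, the assumed correlation and a range of correlations rather than one figure.

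Preferably make the main comparison a baseline-adjusted (ANCOVA-type) follow-up contrast, with baseline as covariate and not as a level of time. At d = 0.5 and an assumed correlation of 0.5, power is about 93% at N = 82 for the mean of the three follow-ups. For 6 months alone it is 73% (N = 82) to 83% (N = 104), and at low correlations it falls below 80% even with 104, so the range should be shown if that visit is chosen.

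If the ANOVA is kept, replace the 80% with the lower conditional range. Holding 80% at ρ = 0.5 would otherwise take 142 participants for the main effect or 118 for the interaction.

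The cost is a rewritten sample-size paragraph and, for the preferred route, a matching change to the analysis sentence. No extra recruitment is needed for either correction. If the ANOVA stays, the stated power becomes less favourable.
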